## Abstract

**Background:**

Research evidence from observational studies suggests that cognitive activity reduces the risk of cognitive impairment in later life as well as the rate of cognitive decline of people with dementia. The Promoting Healthy Ageing with Cognitive Exercise (PACE) study has been designed to determine whether a cognitive activity intervention decreases the rate of cognitive decline amongst older adults with mild cognitive impairment (MCI).

**Methods/Design:**

The study will recruit 160 community-dwelling men and women aged 65 years of age or over with mild cognitive impairment (MCI). Participants will be randomly allocated to two treatment groups: non-specific education and cognitive activity. The intervention will consist of ten 90-minute sessions delivered twice per week over a period of five weeks. The primary outcome measure of the study is the change from baseline in the total score on the Cambridge Cognitive Score (CAMCOG). Secondary outcomes of interest include changes in memory, attention, executive functions, mood and quality of life. Primary endpoints will be collected 12, 52 and 104 weeks after the baseline assessment.

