Similar to mentally stimulating leisure activities, cognitive stimulation (CS) is a type of intervention that emphasises the benefits of group activities focussing on education, discussion and debate, and problem solving. In contrast, cognitive rehabilitation (CR) can be tailored towards an individual's needs, with consideration given to specific areas of impairment and an emphasis on improving everyday functioning. Another commonly used strategy is cognitive training (CT), which aims to provide the individual with a set of standardised tasks that they repeatedly perform. CT using specifically designed computer programs has become a burgeoning business and is generating increasing scientific interest.

Collectively, the research in this area has revealed that older adults (with and without dementia) show modest gains across areas related to the target intervention, and improvements on subjective measures assessing aspects of mood and quality of life have also been observed [8]. However, there is a paucity of randomised controlled trials in this area, limiting conclusions that can be drawn from existing data.

We have designed a single-blind, randomised controlled trial of an intervention that draws on methods of cognition-focussed approaches, selected with regard to suitability for older adults with MCI, and combined into a package considered interesting, engaging and acceptable to this group. The primary focus of this research is to determine whether a structured program of cognitive activity (CA) can decrease the rate of cognitive decline amongst older adults with MCI over 24 months. We hypothesize that participants allocated to the CA group will experience less cognitive decline than older adults randomised to a control education intervention.

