### Sample Size and Power Calculation

At present there is no reliable data for calculating the sample size of the proposed trial. Currently available data suggests that older people living in the community lose 1.6 points per year on the CAMCOG [30]. Factoring in a possible 20% loss to follow up, with 64 people in each group we will have 80% power to detect a between-groups difference of 1.5 points on the CAMCOG. This assumes a decline that is twice as large in the educational compared with the cognitive intervention group, and although statistically this may be associated with moderate effect size (0.5), it is the minimum difference that one would consider clinically significant.

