### Analysis of the Data

Changes in the CAMCOG score from baseline are the primary outcome of interest in the study. We will model these changes at 3 time points: 12 weeks (immediately after the intervention comes to an end), 52 and 104 weeks. We will use mixed effects models to analyse the data. This approach will enable us to take into account the cognitive performance of participants at baseline, as well as the intra-person correlation generated from repeated measures. Intention-to-treat analyses will be based on the use of imputation by chain equations (ICE), which will precede the use of the mixed-effects model.

We accept that participation in the cognitively non-specific educational intervention is likely to have an effect on the performance of participants. However, to ensure continued participation of the control group we deemed it crucial to provide some form of intervention or potentially face differential drop out, with the control group participants withdrawing because of lack of engagement in the study. We will model changes over time for both groups and this will enable us to determine the effect of both interventions (as well as the sustainability of this effect over 24 months) on cognitive performance.

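### Weeks 12, 52 and 104 are all labelled primary and left unranked, although the hypothesis and the sample size point to one contrast at 24 months

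*Protocol article*

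**What the plan says.** The outcome variable is single and clear: change from baseline in total CAMCOG score. The timing is not. The Methods/Design part of the abstract states "Primary endpoints will be collected 12, 52 and 104 weeks after the baseline assessment". The section Analysis of the Data repeats the three visits on an equal footing: "We will model these changes at 3 time points: 12 weeks (immediately after the intervention comes to an end), 52 and 104 weeks". It then says "We will use mixed effects models to analyse the data", without identifying the contrast from that model that decides the trial.

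The last paragraph of the Background sets the question: whether the programme "can decrease the rate of cognitive decline amongst older adults with MCI over 24 months".

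Sample Size and Power Calculation starts from the premise that "older people living in the community lose 1.6 points per year on the CAMCOG". It assumes twice as much decline with education as with cognitive activity (CA), and concludes that "with 64 people in each group we will have 80% power to detect a between-groups difference of 1.5 points on the CAMCOG", with a standardised effect of 0.5. No visit is attached to the 1.5 points.

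**The concern.** The article gives the same primary label to three visits that do not answer the same question. Week 12 is described as the point at which the intervention has just ended. Baseline is placed about two weeks before the first session and the sessions last five weeks, so week 12 falls some five weeks after the last session. A difference there would mainly show what strategy training does to test performance in the short term. It says little about the rate of decline over two years. Week 104 is also the only one of the three visits that follows both the booster call at six months and the group booster offered after the 12-month assessment.

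If the deciding contrast is left open, it can be chosen after the results are known. An early gain that has gone by 24 months could then be presented as a primary success while the 24-month hypothesis is unsupported. If the three visits were tested separately with no adjustment, the false-positive rate of the primary claim would also exceed its nominal level.

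**Working it through.** **Inputs from Sample Size and Power Calculation:** difference 1.5 points; standardised effect 0.5; 64 per group; 80% power; 20% loss; decline of 1.6 points per year; decline with education twice that with CA. The implied SD is 1.5/0.5 = 3.0.

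**Assumed, because not stated:** two-sided alpha of 0.05; equal correlation of 0.4 to 0.8 between the test statistics of the three visits; the 1.6 points per year is the education group's rate, so CA loses 0.8.

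**1. The plan's own figure.** n per group = 2 × (1.960 + 0.842)² × 3.0² / 1.5² = 62.8, so 63. The t-test version gives 63.8, so 64. Power at 64 per group is 0.807 (normal) or 0.801 (t-test). Allowing for 20% loss, 64/0.8 = 80 per group, or 160 in total. The sample size reproduces as one two-sided 5% comparison. A one-sided 5% test would need only 50 per group.

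**2. Which visit the figure fits.** The expected difference after w weeks is (1.6 − 0.8) × w/52. The standard error is 3.0 × √(2/64) = 0.530. Power is Φ(difference/SE − 1.96) plus the opposite tail, which matters only at week 12.

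| Visit | Expected difference | Difference/SE | Power |
|---|---|---|---|
| Week 12 | 0.8 × 12/52 = 0.18 | 0.35 | about 6% (5% in favour of CA) |
| Week 52 | 0.8 | 1.51 | about 33% |
| Week 104 | 1.6 | 3.02 | about 85% |

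Only week 104 gives a difference near 1.5 points and power of at least 80%. If 1.6 per year were instead the CA rate and 3.2 the education rate, the difference would be 1.6 × 12/52 = 0.37 at week 12, 1.6 at week 52 and 3.2 at week 104. The 1.5 points would still fit only one visit, and not week 12.

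**3. Error rate if each visit were tested separately at two-sided 5%.** With independent tests the rate is 1 − 0.95³ = 14.3%. With equally correlated normal statistics (2,000,000 simulated draws):

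| Correlation | Any false positive | Any in favour of CA |
|---|---|---|
| 0.4 | 13.1% | 6.6% |
| 0.6 | 11.8% | 5.9% |
| 0.8 | 9.8% | 4.9% |

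A single test gives 5% and 2.5%. One joint or slope test also stays at 5%.

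**4. A purely transient gain.** Suppose the true effect is 0.5 SD at week 12 and nil later. The shift in the week-12 statistic is 0.5 × √(64/2) = 2.83. The chance of at least one significant result in favour of CA across the three visits is then about 81%, against 2.5% at week 104 alone.

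**5. Keeping three co-equal visits with a Bonferroni correction.** Alpha per visit is 0.05/3 = 0.0167. For 1.5 points, power per visit at 64 per group falls to 66.8% (t-test 65.6%). Restoring 80% needs 84 per group (t-test 86). With 84, that is 84/0.8 = 105 per group, or 210 in total, after 20% loss.

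**The case against.** A reader might infer that the plan lets a significant difference at any one visit count as success, so that three unadjusted tests are built in. The article does not say this. It names one primary outcome measure, and the sentence in the abstract can be read as a visit schedule. The analysis section describes a repeated-measures model of change over time, which could deliver one joint or slope test. It contains no rule for separate tests by visit. That objection stands, so the error rates in steps 3 and 4 are conditional. The headline 10% to 13% also counts errors in both directions, and the part favouring CA is half of that.

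It can also be said that alpha, multiplicity rules and the model contrast belong in an analysis plan that is not shown. This is fair as regards their absence, and no fault is found on that ground. What remains is what the article does state: it gives three visits the primary label, and this does not match its own hypothesis or its single-comparison sample size.

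The analysis section also intends to examine whether effects last for the full 24 months, so a fading gain would be visible. That helps interpretation but does not stop the early gain from being called primary.

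Finally, a slope contrast answers a question about rate at least as directly as a 104-week difference, which can include a retained training gain. This stands, and the fix allows for it.

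**Conclusion.** The point holds as a mismatch within the document. Three visits are designated primary without ranking, while the hypothesis concerns 24 months and the planning figures reach about 1.5 points with about 80% power only there. This rests on the implied SD of 3.0, two-sided 5%, and 1.6 points per year as the education group's rate.

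It does not hold as a claim that the plan inflates type I error. If the visits were tested separately, the chance of at least one false positive would be about 13% to 10% for correlations of 0.4 to 0.8, of which 6.6% to 4.9% would favour CA against 2.5% for one test. A single joint or slope test would carry no inflation. The risk of an early gain being reported as the primary result does not depend on those error rates, because even a perfectly adjusted success at week 12 alone would not support the 24-month hypothesis.

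**What to change.** State one primary contrast: the between-group difference in CAMCOG change from baseline at 104 weeks, estimated from the mixed model using all visits, at two-sided 5%. If the sponsor prefers, the group-by-time slope to 104 weeks can take its place, but only one of the two should be named. List the 12- and 52-week differences as secondary, and reword the sentence in the abstract to match. Attach the 1.5 points in the sample size section to the chosen contrast. Fix this before any results by group are seen.

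The cost is a sentence or two. For the 104-week difference the existing calculation still applies, so 64 per group (160 recruited) stands, and data collection is unchanged. The sponsor gives up the option of claiming primary success on an early visit alone. The alternative of three co-equal visits with Bonferroni would need about 210 participants, whereas 160 have already given consent according to the Clinic Screen section.

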**Discussion:**

The proposed project will produce the best available evidence on the merits of increased cognitive activity as a strategy to prevent cognitive decline among older adults with MCI. We anticipate that the results of this study will have implications for the development of evidence-based preventive strategies to reduce the rate of cognitive decline amongst older people at risk of dementia.

**Trial registration:**

ACTRN12608000556347

## Background

The World's population is ageing rapidly and so is the frequency of age-related disorders. Dementia is one of the most frequent mental health disorders of older people and a leading cause of years of life lost due to disability [1]. Mild Cognitive Impairment (MCI) in old age is considered an important clinical state potentially predictive of future cognitive decline. The term MCI has been used to describe a heterogeneous group of older adults, who, whilst not fulfilling diagnostic criteria for dementia, demonstrate cognitive abilities at a level below what is considered normal for their age. Cognitive deficits may be apparent across unitary or multiple domains though the person continues to maintain a high level of functional independence [2]. Whilst this diagnostic group is at increased risk for conversion to dementia, a substantial number of individuals remain stable or even return to normal levels of functioning with time [3].

There is increasing evidence that the onset of dementia can be delayed by targeting relevant risk factors. In older adults, frequent participation in mentally stimulating leisure activities has been associated with stronger cognitive abilities (such as memory) and reduced risk of dementia [4,5]. The idea that mentally stimulating activity can influence cognitive processes is akin to the "use it or lose it" adage [6]. Few randomised controlled studies have explored this notion and critical evaluation of the research on this topic reveals a number of methodological limitations. These include the specific nature of some of the participant cohorts, the tests used to measure cognitive functioning, and the complexity associated with identifying and defining a broad range of leisure activities with regard to type and degree of cognitive stimulation (see [6] for a review).

Cognition-focused interventions (cognitive training, cognitive rehabilitation and cognitive stimulation) attempt to make use of intact domains to help maintain cognition and prevent/delay decline. These techniques have also been employed to increase functional independence and reduce caregiver burden (see [7] for a review).

Similar to mentally stimulating leisure activities, cognitive stimulation (CS) is a type of intervention that emphasises the benefits of group activities focussing on education, discussion and debate, and problem solving. In contrast, cognitive rehabilitation (CR) can be tailored towards an individual's needs, with consideration given to specific areas of impairment and an emphasis on improving everyday functioning. Another commonly used strategy is cognitive training (CT), which aims to provide the individual with a set of standardised tasks that they repeatedly perform. CT using specifically designed computer programs has become a burgeoning business and is generating increasing scientific interest.

Collectively, the research in this area has revealed that older adults (with and without dementia) show modest gains across areas related to the target intervention, and improvements on subjective measures assessing aspects of mood and quality of life have also been observed [8]. However, there is a paucity of randomised controlled trials in this area, limiting conclusions that can be drawn from existing data.

We have designed a single-blind, randomised controlled trial of an intervention that draws on methods of cognition-focussed approaches, selected with regard to suitability for older adults with MCI, and combined into a package considered interesting, engaging and acceptable to this group. The primary focus of this research is to determine whether a structured program of cognitive activity (CA) can decrease the rate of cognitive decline amongst older adults with MCI over 24 months. We hypothesize that participants allocated to the CA group will experience less cognitive decline than older adults randomised to a control education intervention.

## Methods/Design

### Background

The Promoting Healthy Ageing with Cognitive Exercise (PACE) study is a randomised controlled trial that commenced recruitment of participants in March 2007.

In late 2006, eight individuals with MCI, aged 60 years and over, were invited to offer their opinions regarding the development of a program of cognitive activity (CA), specifically designed for older adults with cognitive decline. The group confirmed the merit of such research and provided feedback with respect to the elements needed to be incorporated into the designed intervention. The general consensus was that any CA program needed to be challenging, personally stimulating and to have a social component.

In February 2007, the CA and educational interventions forming the basis of the PACE study were piloted with 10 participants (five allocated to each intervention), aged 65 and over with MCI. These individuals attended on a daily basis over a two week period and were asked to provide written feedback regarding the session material. The proposed interventions were well received, with positive feedback regarding the relevance of the content/material, format and delivery style. The education group described the program as "useful" and "informative" and the CA group, "encouraging" and "practically helpful". After collating the feedback, additional, minor modifications were made to the study protocol and recruitment began.

### Participants

#### Recruitment of older persons

Participants were community dwelling volunteers recruited from various sources such as memory clinics, local media and other ongoing research studies. Potential participants were initially screened with a semi-structured interview over the telephone and invited to visit the Western Australia Centre for Health and Ageing (WACHA), Royal Perth Hospital (RPH) for a more detailed screening assessment (clinical screen) and to provide written informed consent. The Ethics Committee of the RPH has approved the study protocol and procedures.

#### Inclusion and Exclusion Criteria

The most important defining feature of participants included in the PACE study was a diagnosis of MCI, which was ascertained at a screening assessment at the WACHA (discussed in further detail below). Individuals needed to be aged 65 years or over at their last birthday and be willing and able to travel to the WACHA. All were proficient in spoken and written English. Individuals with a diagnosis of dementia according to ICD-10 criteria for Research [9] or suffering notable cognitive impairment, as evidenced by a Mini Mental State Examination (MMSE; [10]) score of 23 or less, were excluded from the study. Additional exclusion criteria included current psychiatric disorder (e.g. depressive episode), and current history of hazardous or harmful alcohol consumption (based on the Australian Alcohol Guidelines endorsed by the National Health and Medical Research Council 2001). Those individuals with a current medical condition that prevented participation in the study tasks (such as sensory impairment) or was associated with reduced survival over a 12 month period (e.g. advanced cancer) were excluded. We also excluded from the trial people who reported a clinical history of stroke associated with permanent disability.

#### Telephone Interview

Volunteers were initially screened via a telephone interview to ascertain individuals' concerns regarding their memory. Those indicating that they had received a diagnosis of dementia were immediately excluded. The remainder were then asked about general health - both past and current concerns - as well as education and English literacy skills. Details regarding current alcohol consumption were also collected and all potential participants completed the PHQ-9 (see below) and the TICS-M (see below). Telephone interviews took approximately 10 to 30 minutes to complete depending on the extent of information needed to address inclusion and exclusion criteria. Those meeting provisional criteria for inclusion were invited to a face-to-face assessment at the WACHA to confirm that they fulfilled the study criteria.

##### Patient Health Questionnaire - Nine Item (PHQ-9) [11]

The PHQ-9 is the depression module taken from the full PHQ [12], an instrument used to make criteria-based diagnoses of depressive and other mental disorders according to the DSM-IV. In this study it was used to initially exclude individuals with depression and then to monitor the presence of depressive symptoms at follow up. Scores range from 0 to 27, with scores of 15 or greater indicative of clinically significant depression. Volunteers with a score of 15 or more on the PHQ-9 were excluded from further participation in the study.

##### The modified Telephone Interview for Cognitive Status (TICS-M)_[13]

The TICS-M was developed as a dementia screen and contains 21 items, with a total score out of 50. It takes five to ten minutes to complete and has been used to recruit for clinical trials by screening for amnestic MCI. In this study, individuals who obtained scores between 19 or greater and 38 or less were considered as possible candidates with MCI and invited to complete the next phase of recruitment. Older adults with scores lower than 19 were excluded, with this score suggesting the presence of clinically significant cognitive impairment. Those individuals with scores above the cut-off were also excluded as their performance suggested relatively intact cognitive functioning.

#### Clinic Screen

Three-hundred and twenty-four older adults completed the face-to-face assessment to establish the diagnosis of MCI according to the following criteria [2]

• Cognitive complaints and reports of decline from the individual

• Cognitive disorder as evidenced by clinical evaluation (impairment in memory and/or in another cognitive domain)

• Absence of major repercussions on daily life (the individual may however report difficulties concerning complex day to day activities)

• Absence of dementia

Cognitive disorder was established by identifying performances 1.5 standard deviations below the age and sex norms on any Consortium to Establish a Registry for Alzheimer's Disease (CERAD) cognitive task [14]. The CERAD is composed of sub-tests assessing language, memory and praxis and is considered a valid and reliable measure of cognitive function, as well as MCI and Alzheimer's disease [15]. Embedded within this test battery is the MMSE. This brief cognitive test is a commonly used screening instrument that produces a total score that can range from 0 to 30. Scores lower than 24 are reliably associated with the diagnosis of dementia or other organic mental disorders. The present study also used the MMSE to exclude participants with more severe cognitive impairment than MCI.

In addition to the cognitive screen, participants were required to score less than 16 on the World Health Organisation's Alcohol Use Disorders Identification Test (AUDIT). This self report questionnaire is considered a reliable screening tool sensitive to the detection of risky, hazardous or harmful drinking [16]. There are 10 items and supplementary questions, with questions scored on a scale of 0 to 4. Scores of 16 or above suggest "high-risk" or "harmful level" of drinking behaviour.

A self-reported medical history questionnaire was also completed by the participants and details collected regarding their medication use. A screen of participants' ability to manage complex activities of daily living was conducted using a modified version of the Structured Assessment of Independent Living Skills (SAILS [17]). Information regarding the participant's motor skills (fine and gross), language abilities and capacity to carry out tasks similar to day to day activities (e.g. money related skills, following a recipe, reading a calendar) were collected. A score of 150 represented a perfect score and those individuals with scores of less than 141, suggestive of difficulties carrying out instrumental activities of daily living, were excluded.

The screening assessment at the WACHA took approximately 30 to 40 minutes to complete. Any pertinent clinically information was reported to the relevant treating physician with the consent of the study participant. Of those who were screened, 171 met criteria and 160 completed written informed consent to participate.

